## Methods

### Settings

The study will take place within the administrative districts of Nepal (Jhapa administrative district) and Nigeria (Ibadan North, Ibadan North West, Ona Ara, and Akinyele local government areas). In each country, a minimum of 6 PHCs will be recruited for the study to represent a range of urban and rural settings.

Nepal is classified as a lower-middle-income country, with an estimated population of 28.1 million [19]. In a recent survey, 16.8% of individuals attending primary care facilities met the criteria for depression [20]. However, only 8.1% had sought care for their mental health [21]. Primary care facilities include PHCs, health posts, urban health centers, community health units, and primary

health care outreach clinics. In these facilities, services are delivered by medical officers, health assistants, staff nurses, auxiliary health workers, and auxiliary nurse midwives. However, medical officers and staff nurses are only available in PHCs [22]. The availability of mental health care in the country is limited to services largely provided through hospitals located in the larger cities [22]. The Jhapa administrative district has a total population of 812,650 people. Medical care is provided through 1 zonal hospital, 6 PHCs, 44 health posts, and 6 urban health centers [23]. Specialist outpatient mental health services are located in 2 private hospitals within the district. The mhGAP-IG was adopted by the government of Nepal and implemented in several districts after the major earthquake in 2015. The government has allocated a budget for district-level mental health care services to include the addition of 6 psychotropic drugs to those already freely available within health facilities and the strengthening of community mental health care services [24].

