## Statistical Power and Sample Size Calculation

The study will take place in 1 government administrative region in Nepal and 4 in Nigeria. We will identify approximately 20 PHCs in Nepal and 6 in Nigeria. In each country, half of the PHCs will be randomly allocated to either the e-version or the paper version of the mhGAP-IG. As the clinics vary in size, we will assess at least two staff members in each clinic, with an estimated 2-5 health workers per facility and an overall enrollment of 40 PCWs in Nepal and 30 PCWs in Nigeria. Regarding patient numbers, on the basis of the sample size for the study by Sangha et al [34] on smartphone app for improving cognition to improve case detection, we will conduct within-arm comparison detection rates if at least 40 patients screen positive on the Patient Health Questionnaire (PHQ-9) in the research assistant interview in the 1-month pretraining period and in the first month of the posttraining patient enrollment period, which begins after 3 months of intensive supervision. This will allow us to detect a within-arm increase in the clinical case identification rate of 43% for the e-mhGAP-IG after the implementation of the e-version with 90% power at the 5% level of significance, assuming an intraclass correlation coefficient of 0.02. For example, with a 10% detection rate pretraining, 2 patients would receive a health worker depression diagnosis out of 20 patients screening positive. After training, the detection rate would increase to 53%, which equates to 11 patients diagnosed by a health worker out of 20 patients screening positive.

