## Patient Data

In the month before mhGAP-IG training, the research team will collect depression diagnosis and treatment initiation data from patient baseline interviews and clinical notes at participating clinics. These data will be used as a baseline assessment of the accuracy of diagnosis and the adequacy of treatment initiation. Patients attending PHC 3-8 months following PCW mhGAP-IG training will be interviewed by a trained member of the research team either immediately before or after their clinic appointment. Quantitative measures will be used to assess depression, disability, intervention acceptability, and therapeutic alliance during individual interviews with a member of the research team as follows:

1. Depression: The PHQ-9 [49] is a self-administered diagnostic instrument for depressive disorders. The *Diagnostic and Statistical Manual of Mental Disorders, Fourth Edition* criteria for depression are scored as 0 (not at all) to 3 (nearly every day). A PHQ-9 score  $\geq 10$  had a sensitivity of 94% and 85% and a specificity of 80% and 99% for major depression in Nepal [50] and Nigeria [51], respectively.

2. Disability: Data on sociodemographic information (sex, age, education, marital status, and work status) will be collected through questions A1-A5 of the World Health Organization Disability Assessment Schedule 2.0 (WHODAS 2.0) [52]. The WHODAS 2.0 is a generic assessment instrument assessing health and disability across 6 domains (cognition, mobility, self-care, getting along, life activities, and participation). The research team will use the 12-item interviewer-administered version. The WHODAS 2.0 has been adapted and validated for use in Nepal [53-55] and Nigeria [56].
3. Treatment initiation: Treatment details will be extracted by the research team from patient records to document how diagnosis matches up with treatment and treatment modifications during care.
4. Therapeutic alliance: The ENACT-service user version [47] is a 15-item measure of patient experience of care and perception of therapeutic engagement. Example items include clear explanations, names for health problems, understanding and empathy, and expectations for recovery.

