#### PCW and Patient Outcome Analysis

The primary outcome will be the accuracy of the depression diagnosis. The research team will identify a patient as screening positive based on the PHQ-9 result immediately before or after the patient sees the PCW. *Screening positive* will be defined as scoring  $\geq 10$  on the PHQ-9. The research team will also assess sensitivity to change, for change in both the PHQ-9 and WHODAS 2.0 scores from baseline and 3 months after initiation of treatment. *Positive diagnosis* will be defined as a clinical diagnosis of depression documented by the health worker in the clinical notes. *Accurate detection* will be defined as PHQ-9  $\geq 10$  and a health worker depression clinical diagnosis. We will also report findings in terms of the sensitivity and specificity of health worker diagnoses. *Sensitivity* will be defined as the proportion of health worker–diagnosed patients who had PHQ-9 above the cutoff, out of all patients who scored above the PHQ-9 cutoff. *Specificity* will be defined as the proportion of patients who did not receive a health worker depression diagnosis and scored below the PHQ-9 cutoff, out of all patients scoring below the PHQ-9 cutoff.

Features of the cRCT design will be accommodated in all analyses, and an intention-to-treat approach will be used. The principles of analysis will be (1) the PHC-level accuracy outcome is binomial (ie, number of accurate diagnoses out of all diagnoses based on patient-level data), and therefore, a generalized linear mixed model will be used (specifically, a log-binomial regression to obtain probability ratios); (2) accuracy is a cumulative measure, and therefore, there are no repeated measures over time; and (3) missing data can occur at either the health worker or patient level.

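### The log-binomial accuracy outcome takes all diagnoses as its denominator, which makes it a positive predictive value, while the power statement and the other analysis text use detection among PHQ-9-positive patients

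*Protocol*

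**What the plan says.** All references are to the protocol.

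- *PCW and Patient Outcome Analysis* opens: "The primary outcome will be the accuracy of the depression diagnosis". For a detection to count as accurate, both results are needed: it "will be defined as PHQ-9 $\geq 10$ and a health worker depression clinical diagnosis". For a diagnosis to count as positive, the worker's entry alone is enough: it "will be defined as a clinical diagnosis of depression documented by the health worker in the clinical notes".
- The same section treats clinic-level accuracy as binomial, the "number of accurate diagnoses out of all diagnoses based on patient-level data", to be fitted by a generalized linear mixed model, "specifically, a log-binomial regression to obtain probability ratios".
- It also promises sensitivity (denominator: everyone above the PHQ-9 cutoff) and specificity (denominator: everyone below it). Its closing paragraph compares detection among patients scoring 10 or more in a separate linear mixed model.
- *Statistical Power and Sample Size Calculation* plans on detection among screen-positives: "with a 10% detection rate pretraining, 2 patients would receive a health worker depression diagnosis out of 20 patients screening positive", rising to 53%, or 11 of 20.
- *Implementation Outcome Analysis* names the primary outcome as the change in the PHQ-9 detection rate.

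**The concern.** Apart from the reported specificity, the other quantities in the plan are conditional on the patient being PHQ-9 positive: of those who screen positive, how many does the worker diagnose? The log-binomial model conditions on the worker having made a diagnosis: of those diagnosed, how many screen positive? The second quantity cannot register a missed case, and missed cases are what better detection reduces.

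Two further problems follow. The denominator is itself changed by training, so before and after are compared on differently selected patients. Before training it is also very small, because few patients are diagnosed.

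The Abstract makes accurate identification of depression the primary outcome of the later full trial, and *Study Design* says these data will be used to power it. An estimate taken from this model would not describe the quantity on which the present calculation was planned.

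**Working it through.** **1. The plan's own figure.** Inputs from *Statistical Power and Sample Size Calculation*: 10% versus 53%, 90% power, 5% significance, intraclass correlation 0.02. With unpooled variance and a two-sided test:

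n = (0.10×0.90 + 0.53×0.47) × (1.960 + 1.282)² / 0.43² = 0.3391 × 10.51 / 0.1849 ≈ 19.3 per period.

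Assume 2 positives per clinic (20 positives over 10 clinics per arm in Nepal). The design effect is 1 + (2 − 1)×0.02 = 1.02, so n ≈ 19.7, or 20. Power at 20 per period is about 90.5%. The stated 90% is therefore reproduced with 20 PHQ-9-positive patients per period, and **its denominator is PHQ-9 positives**. Other test forms at n = 20 give 80% (Fisher exact) to 92% (pooled, one-sided). The choice of test does not affect this point.

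**2. What the log-binomial outcome is.** Let TP be patients with PHQ-9 ≥10 and a worker diagnosis, and FP those with PHQ-9 <10 and a worker diagnosis. By the protocol's definitions, accurate diagnoses = TP and all diagnoses = TP + FP.

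- Modelled outcome: TP / (TP + FP), the positive predictive value (PPV).
- Detection: TP / (all PHQ-9 ≥10).

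**3. The plan's counts in both.**

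| Quantity | Before | After | Ratio |
|---|---|---|---|
| Detection | 2/20 = 10% | 11/20 = 55% (planned 53%) | 5.5 (planned 5.3) |
| PPV, no false positives | 2/2 = 100% | 11/11 = 100% | 1.0 |
| PPV, false positives in proportion | 2/(2+2) = 50% | 11/(11+11) = 50% | 1.0 |

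The last row is general: if TP and FP are both multiplied by k, then kTP/(kTP + kFP) is unchanged, at any prevalence.

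**4. Constant false-positive rate.** The protocol gives no health worker false-positive rate, so 0.5% to 2% is assumed, the same before and after. *Participants* gives 200 screened per arm per country per month. Detection goes from 10% to 53%. The PHQ-9-positive share is assumed to be 16.8% (the Nepal prevalence in *Settings*), 10% (20/200), or 5.5% (the Nigeria prevalence in *Settings*).

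| PHQ-9 positive | False-positive rate | PPV before | PPV after | Ratio |
|---|---|---|---|---|
| 16.8% (33.6/200) | 0.5% | 3.36/(3.36+0.83) = 80% | 17.8/(17.8+0.83) = 96% | 1.19 |
| 16.8% | 1% | 3.36/(3.36+1.66) = 67% | 17.8/(17.8+1.66) = 91% | 1.37 |
| 16.8% | 2% | 3.36/(3.36+3.33) = 50% | 17.8/(17.8+3.33) = 84% | 1.68 |
| 10% (20/200) | 0.5% to 2% | 69% to 36% | 92% to 75% | 1.34 to 2.09 |
| 5.5% (11/200) | 0.5% to 2% | 54% to 23% | 86% to 61% | 1.60 to 2.69 |

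Every ratio is well below 5.3. In the 16.8% and 1% case, the pretraining denominator is only 3.36 + 1.66 ≈ 5 diagnoses per arm-month.

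**5. Sensitivity to the 16.8%.** *Settings* says "16.8% of individuals attending primary care facilities met the criteria for depression", which may be true prevalence and not a PHQ-9-positive rate. With the Nepal PHQ-9 sensitivity of 94% and specificity of 80% quoted in *Patient Data*, the positive share would be 0.168×0.94 + 0.832×0.20 = 32.4%, about 65 of 200. The PPV ratio is then:

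- at 0.5%: [34.4/(34.4+0.68)] / [6.49/(6.49+0.68)] = 0.981/0.906 ≈ 1.08;
- at 2%: [34.4/(34.4+2.70)] / [6.49/(6.49+2.70)] = 0.927/0.706 ≈ 1.31.

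The attenuation is greater, so the conclusion does not depend on which reading is right.

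**6. The looser reading of all diagnoses.** Suppose it means all classifications, so that the outcome is overall accuracy. With 20 positives in 200 and specificity held at 99%: (2 + 178.2)/200 = 90.1% before, (11 + 178.2)/200 = 94.6% after, ratio 1.05. True negatives dominate, and the outcome still does not match the power statement.

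**The case against.** The strongest reply is that detection is already covered elsewhere. Sensitivity and specificity are promised with the correct denominators, the closing paragraph of the analysis section models detection among patients scoring 10 or more, and *Implementation Outcome Analysis* names the detection rate. **This stands**, and it limits the point: a reader might infer that a real gain would vanish from the trial report, and the documents do not support that. It does not remove the conflict. The section attaches the log-binomial model to the outcome it calls primary and gives that model the other denominator. The separate detection model is linear with repeated measures, whereas the accuracy principles say there are no repeated measures, so it does not restate the same analysis.

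Second, no change is not the expected result. **This also stands.** A flat ratio needs zero or proportionally rising false positives. A falling one needs false positives to rise faster than true positives, and nothing in the protocol suggests that they will. At a constant rate above zero the PPV rises, but by much less than detection.

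Third, this is a feasibility study: the Abstract makes feasibility and acceptability primary, detection is a secondary intervention outcome, and no progression criterion uses accuracy. That lowers the stakes for this trial. It does not help the later trial that these data are meant to inform.

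A reader might also infer that imperfect PHQ-9 accuracy puts a low ceiling on the modelled outcome. It does not. In Nepal, a clinician who diagnosed exactly the true cases would score the PHQ-9's own sensitivity, 94%. PHQ-9 error bears on detection among screen-positives, but there PHQ-9 ≥10 is a declared operational definition. Correcting for misclassification is an optional analysis whose absence is no error in the protocol.

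**Conclusion.** The point holds in a limited form. As written, the log-binomial accuracy outcome is a positive predictive value. It contradicts the detection denominator behind the power statement and the other analysis text. For a planned 5.3-fold rise in detection, the modelled ratio would be 1.0 with no or proportionally rising false positives. With a constant false-positive rate of 0.5% to 2%, it would be about 1.2 to 1.7 at 16.8% PHQ-9 positive and 1.6 to 2.7 at 5.5%.

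The false-positive rates and the use of the quoted prevalences as PHQ-9-positive shares are assumptions. The mismatch of denominators is not: it follows from the protocol's definitions. The fault lies in this one model and does not extend to the reported sensitivity, the reported specificity or the separate detection comparison.

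**What to change.** In *PCW and Patient Outcome Analysis*, restate the binomial outcome as the number of patients with a documented health worker depression diagnosis out of all screened patients with PHQ-9 ≥10. Keep specificity among those scoring below 10 as its paired measure, so that a gain in detection is read together with any rise in false positives. Report positive predictive value descriptively, with its numerator and denominator. Use the same definition wherever detection or accuracy is called the primary outcome.

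The cost is a few words in the analysis section. The screening result and the documented diagnosis are already collected for each screened patient, so no new data and no change to the sample size are needed.

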#### Patient Data

We estimate screening a minimum of 400 patients at each site during the pretraining enrollment period and 1200 patients in the posttraining enrollment period (starting 3 months after the mhGAP-IG training). In the posttraining period, we will include a subset of patients who have received a health worker depression diagnosis to follow-up for treatment outcomes. We will follow up with them at approximately 3 months after they are screened to measure their treatment outcomes. A subset of patients will also participate in FGDs to assess their perspectives on the acceptability (AIM) and appropriateness (IAM) of the intervention 3 months after their baseline health care appointment.

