#### Analysis

#### Implementation Outcome Analysis

Quantitative data will be assessed using generalized linear mixed models, depending on the distribution of the outcome (continuous, binary, and count). Descriptive statistics of the implementation survey data (FIM, AIM, and IAM) will be provided. The association between the primary outcome (changes in the PHQ-9 detection rate) and implementation survey data will be analyzed using linear mixed models at 3 and 8 months post training. A 2-level hierarchical model will be used, and all time points will be included as repeated measures in the model at baseline and at 3 months post training and 8 months post training to improve power and account for clustering of observations at patient and PCW levels. These models use maximum likelihood estimation and thus allow for missing outcome data under the missing at random assumption. Associations between secondary outcomes (eg, knowledge, attitudes, and competency) and implementation survey data will be assessed with a similar methodology for the primary outcomes, using generalized linear mixed models depending on the type of outcome (eg, normal, binary, and count). All analyses will be conducted using STATA V.15.1. (StataCorp).

Qualitative data will be assessed using thematic analyses [62]. Thematic analysis consists of 5 stages: familiarization, generating codes, constructing themes, revising themes, and defining themes [63]. Draft codebooks for each participant group (eg, PCWs, supervisors, and patients) will be developed on an initial subset of transcripts by 2 researchers at each site. Following refinement based on researcher consensus, the final codebooks will be used to code each transcript independently by 2 researchers at each site. Subcategories will be assessed for the number of occurrences across all transcripts and themes and categories relevant to the data identified. The findings will be triangulated with quantitative data on implementation and provider and patient outcomes to assess the feasibility and impact of the e-mhGAP-IG.

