Differences in detection rates will be assessed using patient outcome data at 3 months after enrollment, only in depression cases identified in each arm (ie, scoring  $\geq 10$  on the PHQ-9), and the health worker clinical diagnosis. A 3-level hierarchical model will be used when all time points will be included as repeated measures in the model to improve power and take into account clustering of the observation at patient and PHC levels. The 3-level linear mixed model will be used to estimate a 95% CI for the comparison of clinical diagnosis and PHQ-9 screening positive rates (as well as a subanalysis with PHQ-9 plus WHODAS 2.0 criteria) within electronic and paper mhGAP-IG versions. Secondary outcomes (eg, knowledge and attitudes) will be assessed within each arm with a similar methodology for the primary outcomes, using generalized linear mixed models depending on the type of outcome (normal, binary, and count). Clinical feasibility will also be triangulated using penetration and costing data.

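### The protocol gives two incompatible analyses of depression detection, and the one built on 3-month data cannot yield the before-after change that the protocol powers

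*Protocol*

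**What the plan says.** The Abstract and the section Statistical Power and Sample Size Calculation set the target: the detection rate before training against the rate after training, within each arm.

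Two consecutive parts of PCW and Patient Outcome Analysis then say how detection will be analysed.

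- The first treats accuracy as a clinic-level binomial count of accurate diagnoses out of all diagnoses, fitted by log-binomial regression, because "accuracy is a cumulative measure, and therefore, there are no repeated measures over time".
- The second says "Differences in detection rates will be assessed using patient outcome data at 3 months after enrollment", restricted to patients scoring 10 or more on the PHQ-9. It adds that "A 3-level hierarchical model will be used when all time points will be included as repeated measures in the model", with clustering at patient and PHC level, and that "The 3-level linear mixed model will be used to estimate a 95% CI for the comparison of clinical diagnosis and PHQ-9 screening positive rates" within each version of the guide.

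On follow-up, the Patient Data part of Implementation Data says: "In the posttraining period, we will include a subset of patients who have received a health worker depression diagnosis to follow-up for treatment outcomes". The Patient Data part of Outcome Data instead invites patients who screen positive in the opening 3 months of data collection.

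In Implementation Outcome Analysis, the 2-level model linking detection to the implementation surveys is meant to "account for clustering of observations at patient and PCW levels".

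**The concern.** The two paragraphs disagree on the link and scale (probability ratio or linear), on whether there are repeated measures, and on which visit supplies the data. An analyst could follow either and report a different quantity.

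The second paragraph also conflicts with the design. A result fixed once at the index visit has no 3-month value, and patients enrolled before and after training are not repeated observations of the same people. Followed literally, it would analyse only patients who return for follow-up and would have no pre-training comparator.

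The detection estimate matters beyond this trial: the Abstract names detection as the primary outcome of the later full trial, and Study Design says that the data will be used to power it.

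**Working it through.** **1. Reproduce the protocol's own figure.** Inputs from Statistical Power and Sample Size Calculation: detection 10% before and 53% after, 90% power, 5% level, ICC 0.02, and 20 screen-positive patients per period in the worked example. Sidedness is not stated, so two-sided is assumed. I read the threshold of 40 as 20 + 20 within an arm, as in the example.

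Two independent proportions, unpooled variance:

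n = (1.95996 + 1.28155)² × (0.10 × 0.90 + 0.53 × 0.47) / 0.43² = 10.507 × 0.3391 / 0.1849 = 19.27 per period.

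Design effect = 1 + (m − 1) × 0.02, with m = 20 / clinics per arm:

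| Clinics per arm | Source | m | Design effect | n per period |
|---|---|---|---|---|
| 10 | Participants, Nepal (20 PHCs) | 2 | 1.02 | 19.7 |
| 5 | Study Design (10 PHCs per country) | 4 | 1.06 | 20.4 |
| 3 | Participants, Nigeria (6 PHCs) | 6.67 | 1.113 | 21.5 |

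The stated 20 is reproduced to within 2 patients. With a pooled variance, power at 20 versus 20 is 86% before the design effect. In either form the calculation uses two separate groups, one binary result each, no loss to follow-up and no within-patient correlation. It therefore matches an index-visit analysis and not the repeated-measures one.

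**2. When detection is determined.** Under PCW and Patient Outcome Analysis, the PHQ-9 is taken just before or after the patient sees the health worker. Under Participants, the research assistant then checks the case notes for a diagnosis. Both components belong to the index visit, so each patient contributes one yes/no result.

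**3. Who has 3-month data.**

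- Participants describes two enrollment periods: one month before training, and at least 3 months starting 3 months after training. These are separate samples.
- The Figure 1 legend lists one assessment for pre-training patients (P0). The 3-month assessment (P2) is tied to the baseline appointment (P1).
- The Patient Data part of Implementation Data places follow-up in the post-training period.
- The Patient Data part of Outcome Data introduces its follow-up after describing interviews at 3 to 8 months after training.

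Read together, pre-training patients with 3-month data = 0, and no before-after difference can be formed from them. Under the Implementation Data rule, every followed patient already has a diagnosis. If k followed patients scored 10 or more, detection among them is k/k = 100% by construction.

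**4. The denominator in the first paragraph.** Accurate diagnoses over all diagnoses is a positive predictive value. Take the protocol's example (2 of 20 diagnosed before, 11 of 20 after), and suppose F diagnoses in each period fall on patients below the cutoff. F is not given and is assumed equal in both periods. The predictive values are 2/(2 + F) and 11/(11 + F). With F = 0 both are 100% and their ratio is 1. As F grows, the ratio tends to 11/2 = 5.5. The ratio of detection rates is (11/20)/(2/20) = 5.5 whatever F is. The first paragraph's quantity is therefore not the one that the sample size addresses.

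**5. The association model.** Its two levels are patient and PCW. The PHC, which is the randomized unit, is missing, although PCW and Patient Outcome Analysis promises that the cluster design is respected throughout.

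**The case against.** Several points on the other side stand.

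- A reader might infer that the protocol as a whole cannot deliver the before-after change. The documents do not support that. The log-binomial model could deliver it from index-visit data with a period term and the right denominator. The failure belongs to the second paragraph.
- The 3-month wording may be a slip for 3 months post training, when post-training enrollment opens. That is plausible. It would repair the time point, but the text would still need correcting and the conflict over repeated measures would remain.
- The invitation rule under Outcome Data does not expressly exclude pre-training patients, so the figure of 0 rests on reading it with the Figure 1 legend and the Implementation Data text. Even if both periods were followed, the 67% retention threshold under Feasibility Criteria, used only as an illustration, would leave 20 × 0.67 = 13.4, about 13 per period. Power would be about 67% (pooled) to 76% (unpooled) before the design effect.
- A linear model for a binary outcome is not invalid in itself, since it can estimate a risk difference.
- A reader might infer that comparing diagnosis rates with screen-positive rates ignores whether they concern the same patients. The preceding sentence restricts the set to PHQ-9 of 10 or more, where the diagnosed proportion is sensitivity. Sensitivity and specificity are also promised separately.
- A reader might infer that intervals will be too narrow with few clinics. The protocol states no reference distribution, and small-sample corrections are commonly left to the SAP. Nor does it give figures from which the effect of omitting the PHC in the association model could be sized.
- This is a feasibility trial. The Abstract calls detection a secondary outcome, and no progression criterion uses it.

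**Conclusion.** The point holds. The two paragraphs cannot both be followed, and the second, as written, cannot estimate the stated within-arm before-after change: its pre-training sample is 0, on the reading of the follow-up rules set out above. The protocol's 20 versus 20 is sound only as a comparison of two independent index-visit samples (19.3 per period, or 19.7 to 21.5 after the design effect, assuming a two-sided test and unpooled variance). The first paragraph is closer to what is needed but divides by the wrong total.

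This should be fixed. It does not threaten the trial's primary feasibility objective, but detection is the planned primary outcome of the later trial, and the estimate carried forward depends on which paragraph is used.

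**What to change.** Replace both descriptions in PCW and Patient Outcome Analysis with one model:

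- Outcome: health worker diagnosis, yes or no, at the index visit, among patients with PHQ-9 of 10 or more.
- Contrast: pre-training against post-training period, within each arm, as the protocol already intends.
- Clustering: by PHC, letting the period change vary between PHCs where this can be estimated. No patient-level repeated measures.
- Data: index visit only. Keep the 3-month data for treatment outcomes.
- Keep the sensitivity and specificity already promised, and drop all diagnoses as the denominator for detection.

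Reconcile the two Patient Data sections on who is followed up (diagnosed patients or screen-positive patients) and state whether pre-training patients are included. Add the PHC level to the association model in Implementation Outcome Analysis.

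The cost is wording in the analysis and follow-up sections. The detection model needs no new data, and the sample size basis is unchanged.

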**Methods**

A feasibility cRCT will be conducted in Nepal and Nigeria to evaluate the feasibility of the e-mhGAP-IG for use in depression diagnosis and treatment. In each country, an estimated 20 primary health clinics (PHCs) in Nepal and 6 PHCs in Nigeria will be randomized to have their staff trained in e-mhGAP-IG or the paper version of mhGAP-IG v2.0. The PHC will be the unit of clustering. All PCWs within a facility will receive the same training (e-mhGAP-IG vs paper mhGAP-IG). Approximately 2-5 PCWs, depending on staffing, will be recruited per clinic (estimated 20 health workers per arm in Nepal and 15 per arm in Nigeria). The primary outcomes of interest will be the feasibility and acceptability of training, supervision, and care delivery using the e-mhGAP-IG. Secondary implementation outcomes include the adoption of the e-mhGAP-IG and feasibility of trial procedures. The secondary intervention outcome—and the primary outcome for a subsequent fully powered trial—will be the accurate identification of depression by PCWs. Detection rates before and after training will be compared in each arm.

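### The one confidence interval named for detection compares the diagnosis rate with the PHQ-9 positive rate within an arm, not detection before and after training

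*Protocol*

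**What the plan says.** All references are to the protocol.

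- Abstract, Methods: "Detection rates before and after training will be compared in each arm".
- Statistical Power and Sample Size Calculation: the study is sized to "detect a within-arm increase in the clinical case identification rate of 43% for the e-mhGAP-IG". The worked example goes from 10% (2 of 20 patients screening positive) to 53% (11 of 20), so the 43% is a gain in percentage points. Power is 90% at the 5% level with an intraclass correlation of 0.02.
- PCW and Patient Outcome Analysis, first part: "The primary outcome will be the accuracy of the depression diagnosis". Accurate detection is a joint event in one patient: PHQ-9 of 10 or more "and a health worker depression clinical diagnosis". The section adds: "We will also report findings in terms of the sensitivity and specificity of health worker diagnoses".
- PCW and Patient Outcome Analysis, last paragraph: differences in detection are assessed "only in depression cases identified in each arm", explained there as a PHQ-9 score of at least 10, together with the health worker's diagnosis. All time points enter as repeated measures. The model is then to "estimate a 95% CI for the comparison of clinical diagnosis and PHQ-9 screening positive rates", within the electronic and the paper version separately.

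**The concern.** The last clause is the only place where the protocol names an interval for detection, and it sets two rates from the same arm against each other. It mentions neither the time contrast nor the joint event. The quantity the protocol wants is the share of PHQ-9 positive patients whom the health worker diagnoses, after training compared with before.

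A result from this interval could be mistaken for evidence on training. The detection estimates are meant to inform a later full trial whose primary outcome is accurate identification of depression, so the contrast should match that quantity.

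**Working it through.** **1. The plan's own power figure.** Inputs from the sample size section: p1 = 0.10, p2 = 0.53, 20 PHQ-9 positive patients per period, two-sided 5% (sidedness is assumed).

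- SE = sqrt[(0.10×0.90 + 0.53×0.47)/20] = sqrt(0.3391/20) = 0.130.
- Power = Φ(0.43/0.130 − 1.96) = 91.0%.
- With 10 clinics per arm (2 patients each) the design effect is 1 + (2−1)×0.02 = 1.02 and power is 90.5%. With 3 clinics per arm it is 87.9%.

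The stated 90% is therefore reproduced, and it belongs to the before-after contrast in PHQ-9 positive patients. An exact calculation with the pooled z test on that contrast, ignoring clustering, gives 3.9% rejection with no effect (10% vs 10%) and 88% power for 10% to 53% at n = 20. At n = 40 the figures are 5.9% and 99.3%.

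**2. The written contrast in the stated set (PHQ-9 ≥10).** The PHQ-9 positive rate is 1, so the contrast is Se − 1, where Se is sensitivity.

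- 10% detection: 0.10 − 1 = −90 points.
- 53% detection: 0.53 − 1 = −47 points.

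A Wald interval with n = 20 excludes zero when 16 or fewer of the 20 are diagnosed. The exact binomial probability of this is above 99.9% at Se = 0.10 and 99.7% at Se = 0.53. Failed and successful training both exclude zero.

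**3. The written contrast if all screened patients were used.** Let π be the PHQ-9 positive rate and f the false-positive rate, P(diagnosis | PHQ-9 <10).

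- Difference: d = (1−π)f − π(1−Se).
- Paired variance: [b + c − (b−c)²]/n, with b = (1−π)f and c = π(1−Se).
- n = 200 per arm per month (Participants).
- Design effects: Nepal, 10 clinics of 20, 1 + 19×0.02 = 1.38. Nigeria, 3 clinics of 66.7, 1 + 65.7×0.02 = 2.31.

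The protocol gives no f, so 0 to 5% is an assumption. Depression prevalence from Settings (16.8% and 5.5%) stands in for π. Multinomial simulation gives the share of samples whose interval excludes zero. The bracketed figures widen the interval by the design effect without adding clustering to the data, so they are conservative.

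| Country | Se | f | d (points) | Excludes zero |
|---|---|---|---|---|
| Nepal | 10% | 0% | −15.1 | 100% (100%) |
| Nepal | 10% | 5% | −11.0 | 96% (92%) |
| Nepal | 53% | 2% | −6.2 | 86% (77%) |
| Nigeria | 10% | 0% | −5.0 | 99% (67%) |
| Nigeria | 10% | 2% | −3.1 | 40% (7%) |
| Nigeria | 10% | 5% | −0.2 | 6% (0.3%) |
| Nigeria | 53% | 2% | −0.7 | 7% (0.3%) |

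The totals match when f = π(1−Se)/(1−π). At 10% detection this is 0.168×0.90/0.832 = 18.2% in Nepal and 0.055×0.90/0.945 = 5.2% in Nigeria.

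If π for Nepal is built from the protocol's PHQ-9 sensitivity (94%) and specificity (80%), it is 0.168×0.94 + 0.832×0.20 = 32.4%. Exclusion at 10% detection is then 100% for f from 0 to 5%. For Nigeria (85% and 99%) the same step gives 5.6%, and little changes.

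Diagnosing Nepalese patients at random with probability 16.8% gives d = 0 and about 5% exclusion, although sensitivity is only 16.8% and kappa is 0.

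**The case against.** The best defence is that the clause is loosely worded. The paragraph opens with differences in detection, restricts to PHQ-9 positive patients and enters all time points. The interval could therefore be meant for the joint event compared over time, as the Abstract and the sample size section describe. That may be the intent, but the clause has no words for a joint event or a time contrast. If it is the intent, the correction is the same.

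A second defence is that accuracy is covered elsewhere, and part of this stands. Sensitivity is P(diagnosis | PHQ-9 ≥10), and specificity is one minus P(diagnosis | PHQ-9 <10); both will be reported. But neither is given a before-after interval. The log-binomial model takes accurate diagnoses out of all diagnoses, which is a positive predictive value, and it is described as having no repeated measures over time.

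Third, excluding zero is a true statement about under-detection, and the protocol attaches no test to the interval. That is correct. The interval misleads only if it is read as evidence on training.

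A reader might also infer that the interval would show perfect agreement under random diagnosis. The documents do not support this. In the stated set, random diagnosis in Nepal gives 16.8 − 100 = −83 points. With all screened patients, what matches is two totals, while kappa is 0.

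**Conclusion.** The concern holds as a mismatch between the interval written and the quantity planned. In the stated set the contrast is −90 points with no training effect and −47 points with the planned effect, and it excludes zero in at least 99.7% of samples either way at n = 20. This rests only on the protocol's own detection rates. The stated 90% power does not apply to it.

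The all-screened results are secondary and depend on assumed false-positive rates. Exclusion of zero with no training effect is near certain in Nepal at 10% detection and 0 to 5% false positives, but low in Nigeria at about 5%. It should not be presented as certain in both countries.

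Two stronger readings go too far. One is that accuracy and improvement go unexamined: sensitivity, specificity and an accuracy model are planned, and a before-after comparison is stated as an aim. The other is that the trial's conclusions depend on this interval. The trial's main outcomes are feasibility and acceptability, its detection objective is descriptive, and none of the criteria for progression to the full trial uses the interval. This should be fixed, but it does not undermine the study.

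**What to change.** In the last paragraph of PCW and Patient Outcome Analysis:

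1. Replace the contrast with the post- minus pre-training change in P(health worker diagnosis | PHQ-9 ≥10) within each arm, with a 95% CI from a model that allows for clinic clustering.
2. Report the same change for P(health worker diagnosis | PHQ-9 <10), so that a gain in detection can be read beside any rise in false positives.
3. Keep the comparison of diagnosis and PHQ-9 positive totals as a descriptive summary only, and name its analysis set.
4. State that the 90% power refers to item 1.

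The cost is a wording change in the protocol, carried into the statistical analysis plan if there is one. The same patient-level data serve, with no extra patients or visits.
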